## Abstract

**Background:**

Multiple myeloma (MM) is a widely incurable B-cell malignancy that predominantly affects older adults, representing 10% of hematologic cancers. Despite advancements in therapy that have significantly extended median overall survival (OS), MM remains a clinical challenge with poor prognosis for patients refractory to multiple drug classes. There is a critical need for innovative and personalized treatments, including for patients with translocation (11;14), a subgroup characterized by specific therapeutic vulnerabilities. Combined targeting of B-cell maturation antigen (BCMA) and BCL-2 presents a promising personalized treatment strategy for inducing deep remissions and improving outcomes in this specific subgroup.

**Methods:**

The BELI(E)VE trial (NCT05853965) is a German investigator-initiated, prospective, multicenter, open-label phase I/IIa study designed to evaluate the combination of belantamab mafodotin and venetoclax, with or without dexamethasone, in patients with relapsed or refractory multiple myeloma (RRMM) with ≥1 prior treatment line and t(11;14) translocation. The study consists of a dose escalation phase (phase I) to determine the recommended phase 2 dose (RP2D), followed by a dose expansion phase (phase IIa) to assess clinical activity at the RP2D. The phase I portion employs a traditional 3+3 design across four dose levels, while the phase IIa expansion will include 25 additional patients treated at the RP2D. Safety, tolerability, and preliminary efficacy will be evaluated through comprehensive assessments, including assessment for minimal residual disease negativity and ocular exams.

**Discussion:**

The BELI(E)VE trial aims to establish a novel personalized therapeutic approach for a specific subset of MM patients by combining belantamab mafodotin and venetoclax. This combination targets BCMA and BCL-2, potentially inducing deep and durable remissions. The study will provide critical data on the safety and efficacy of this combination, aiming to improve outcomes in t(11;14)-positive RRMM patients. The translational component, examining circulating tumor cells and mitochondrial activity, may identify mechanisms of resistance and response, guiding future personalized therapeutic strategies.

**Trial registration:**

NCT05853965 (2023-04-22).

**Supplementary Information:**

The online version contains supplementary material available at https://doi.org/10.1186/s12885-026-16905-3.

## Background

Multiple myeloma (MM) is a widely incurable B-cell malignancy that accounts for 10% of all hematological malignancies and is the most prevalent hematologic malignancy in patients older than 65 years [1].

Treatment paradigms and outcomes for patients with MM have changed substantially over the past decade with the introduction of effective and tolerable proteasome inhibitor (PI), immunomodulatory agent (IMiD), anti-CD38, and T-cell-redirecting therapies. Recent real-world data from European registries report pooled median overall survival (OS) of 85.5 months across 2012–2023; median OS not yet reached in the 2020–2023 frontline sub-cohort [2]. Nevertheless, a significant unmet need remains for the treatment of relapsed and/or refractory MM (RRMM). Patients who are triple-class exposed (having received at least one PI, one IMiD and a monoclonal anti-CD38 antibody) had an impaired prognosis with a median OS of 13.8 months; and median OS was worse for those refractory to all three classes with 8.6 months [3–5]. Penta-refractory patients (refractory to two PIs, two IMiDs, and an anti-CD38 antibody) have a documented median OS of less than six months [4]. These data underline the unmet need for developing novel treatment options, especially in this pre-exposed patient group.

The prognosis of patients in first-line and relapse treatment is remission-dependent. Achievement of deep remissions is associated with superior outcomes. More recently, emerging data show that achieving minimal residual disease (MRD) negative remissions directly and reliably translates into better progression-free survival (PFS) and OS [6–8]. Hence, MRD negativity has recently been recommended as an early endpoint in MM clinical trials by the Oncologic Drugs Advisory Committee (ODAC) of the U.S. Food and Drug Administration (FDA) [9].

Besides the induction of MRD-negative remissions, the way towards personalized treatment approaches remains an unmet need. Currently, there are no approved biomarker-based therapeutic approaches in the management of MM. Given the multiple available drugs and combination regimens in this disease, predictive biomarkers to guide the selection of therapy would be an essential advancement in the care of these patients, delivering the most effective treatments to the appropriate patient population.

The BELI(E)VE trial therefore moves beyond the prevailing one-size-fits-all sequencing paradigm in myeloma and prospectively tests a genotype-directed combination in a molecularly defined subgroup. To our knowledge, BELI(E)VE is among the first investigator-initiated trials to combine an antibody-drug conjugate with a BCL-2 inhibitor specifically in t(11;14)-positive disease.

### Targeting BCMA and BCL-2 in MM

BCMA (B Cell Maturation Antigen), also designated as tumor necrosis factor receptor superfamily member 17 (TNFRSF17), is expressed on the surface of normal and malignant B lymphocytes [10] and plays an essential role in the development and survival of long-lived bone marrow plasma cells [11]. The restricted expression profile of BCMA makes it an excellent target for a therapeutic antibody with direct cell-killing activity and has limited off-target effects [12]. BCMA-targeted therapies demonstrated impressive results with BCMA-targeted Chimeric Antigen Receptor T cell therapy (CAR-T) [13, 14], BCMA × CD3 bispecific antibodies [15–17], and antibody-drug conjugate (ADC) belantamab mafodotin [18–22]; a total of six BCMA-targeted drugs (2 CAR-T cell constructs, three bispecific antibodies, and one ADC) had received approval in the European Union and the United States for the treatment of relapsed and/or refractory MM (RRMM). While the conditional approval of the ADC belantamab mafodotin was withdrawn following the non-superiority in the DREAMM-3 trial, full approval was granted by EMA in July 2025 based on the significant superiority of belantamab mafodotin in combination with bortezomib and dexamethasone (BVd; median (m)PFS 36.6 months) over daratumumab plus bortezomib and dexamethasone (DVd; mPFS 13.4 months), including an OS benefit [21], and in combination with pomalidomide and dexamethasone (BPd, mPFS not reached) over pomalidomide, bortezomib, and dexamethasone (PVd, mPFS 12.7 months) [22].

Overexpression of BCL-2 (B-cell lymphoma 2) significantly contributes to the pathogenesis of lymphoid malignancies, including MM [23]. Plasma cells are typically geared towards long-term survival and have low apoptotic rates associated with high levels of anti-apoptotic proteins such as BCL-2 and myeloid-cell leukemia (MCL)-1. Dysregulation of apoptotic pathways in these cells, often from aberrant BCL-2 and/or MCL-1 overexpression, is thought to play a significant role in the development and progression of MM. Mainly, myeloma cells with chromosomal translocation t(11;14) express high levels of BCL-2 relative to BCL-X_L_ and MCL-1 [23]. Antagonizing BCL-2 function to induce apoptosis has successfully been done in other hematologic malignancies and is also a compelling therapeutic approach in MM [23–25]. Venetoclax, a potent, orally bioavailable, small molecule inhibitor of the anti-apoptotic protein BCL-2, which restores programmed cell death (apoptosis) in cancer cells, showed durable responses in t(11;14)-positive MM patients in combination with bortezomib and dexamethasone (Vd) [26, 27]. The t(11;14) abnormality is seen in 15% to 20% of myeloma patients and, once present, is stably found over the course of the disease [28–30]. The t(11;14) is currently classified as a standard-risk genetic marker, although it is frequently found in plasma cell leukemia [28–30]. Additionally, dexamethasone, a steroid commonly used in MM treatment, upregulates the expression of the pro-apoptotic molecule BIM (BCL-2 -interacting mediator of cell death) and increases its binding to BCL-2, which results in increased sensitivity to venetoclax [23]. Therefore, combining a potent BCL-2 inhibitor (venetoclax) with low-dose dexamethasone in patients with t(11;14)-positive MM may lead to enhanced antitumor effects given the anticipated synergism between these two drugs (Fig. 1) [31].

**Fig. 1 Fig1:**
[figure not shown]
Modes of action of Belantamab mafodotin and Venetoclax: Belantamab mafodotin targets BCMA on the surface of myeloma cells, leading to its internalization. Subsequently, the cytotoxin mcMMAF is released within the cell, interacting with microtubules by binding to tubulin. This interaction results in cell cycle arrest between the G2 and M phases, ultimately inducing cell death through apoptosis. On the other hand, venetoclax selectively inhibits the Bcl-2 protein, which is overexpressed in t(11;14) positive myeloma cells. Venetoclax’s blockade of Bcl-2 facilitates the programmed cell death of these tumor cells

Both belantamab mafodotin and venetoclax have been and are being investigated in clinical trials in patients with RRMM as monotherapy or in various treatment combinations. However, the combined treatment of an anti-BCMA-directed agent such as belantamab mafodotin with a BCL-2 inhibitor such as venetoclax has yet to be investigated. As both belantamab mafodotin and venetoclax, combined with dexamethasone to further enhance the anti-myeloma effect as depicted above, are candidate treatments inducing deep and long-lasting remissions, including MRD-negativity, the BELI(E)VE trial will evaluate the combination of belantamab mafodotin and venetoclax with and without dexamethasone in t(11;14)-positive RRMM. 

## Methods: study design, patient population, objectives, treatment, and control groups

The BELI(E)VE-Trial (NCT05853965) is an investigator-initiated, prospective, multicenter, open-label phase I/IIa study that consists of a dose escalation phase (phase I) and a dose expansion phase (phase IIa). Up to 49 patients (12–24 in Phase I, 25 in Phase II) are planned for total trial duration over 44 months. Survival follow-up lasts until last patient last visit of the study. Participating hospitals are in Germany and are listed in Supplementary Table S1.

### Patient population

The BELI(E)VE trial recruits adult patients with RRMM and the cytogenetic aberration of translocation t(11;14) due to their higher dependency on BCL-2. Initially, patients were required to have undergone at least four prior treatment lines (in line with the original belantamab mafodotin conditional approval), however following emerging data on the safety and efficacy of belantamab mafodotin combinations in early relapse [22, 32], the trial was amended, and now includes patients from first relapse on (one prior treatment line) who have been exposed to at least one proteasome inhibitor, one immunomodulatory agent and one anti CD38 monoclonal antibody. In addition, patients must have documented evidence of progressive disease on or after the last treatment line and sufficient organ function, as defined in Table 1.

**Table 1 Tab1:** Eligibility (inclusion and exclusion) criteria

Inclusion criteria	Exclusion criteria
1. Subjects must be ≥ 18 years of age.	1. Subject has received prior Venetoclax and/or anti BCMA treatment.
2. Subjects must have an Eastern Cooperative Oncology Group (ECOG) performance status of ≤ 2	2. Participant has used an investigational drug or approved systemic anti-myeloma therapy within 14 days or five half-lives, whichever is shorter, preceding the first dose of study drug. The only exception is emergency use of a short course of corticosteroids (equivalent of Dexamethasone 40 mg/day for a maximum of 4 days) up to 7 days before treatment.
3. Subjects must voluntarily sign and date an informed consent form	3. Participant has had plasmapheresis or radiation therapy within 7 days prior to first dose of study treatment
4. Subjects must have had documented multiple myeloma requiring treatment as defined by the criteria below:Monoclonal plasma cells in the bone marrow > 10% and/or presence of a biopsy proven plasmacytoma at some point in their disease history requiring treatment according to diagnostic criteria (IMWG updated criteria 2014, Rajkumar et al. 2014) with measurable disease at screening (serum M-protein > 500 mg/dL or urine M protein 200 mg/24h, in case of oligosecretory MM serum free light chain > 10mg/dL and abnormal kappa/lambda free light chain ratio)	4. Participant has current corneal epithelial disease except mild changes in corneal epithelium
5. Cytogenetics/FISH confirming t(11;14)	5. Participant has current unstable liver or biliary disease defined by the presence of ascites, encephalopathy, coagulopathy, hypoalbuminemia, esophageal or gastric varices, persistent jaundice, or cirrhosis.Note:Stable non-cirrhotic chronic liver disease (including Gilbert’s syndrome or asymptomatic gallstones) or hepatobiliary involvement of malignancy is acceptable if otherwise meets entry criteria.
6. Prior treatment requirements: - Subjects must have received at least 1 prior treatment line (induction, high-dose, consolidation and maintenance is considered as one treatment line). All patients must have received at least one proteasome inhibitor and at least one immunomodulatory agent and at least one anti CD38 monoclonal antibody. - Subjects must have documented evidence of progressive disease on or after the last treatment line.- Subjects with a history of autologous SCT are eligible for study participation provided the following eligibility criteria are met: i. ASCT was >100 days prior to initiating study treatment, and ii. No active bacterial, viral, or fungal infection(s) present.	6. Participant has a presence of active renal condition (infection, requirement for dialysis or any other condition that could affect participant’s safety). Participants with isolated proteinuria resulting from MM are eligible, provided they fulfil inclusion criteria
7. Subjects must have adequate organ function, defined as follows: a. Hemoglobin ≥8.0 g/dL (without transfusion of red blood cells for the past 14 days) b. Absolute neutrophil count ≥ 1.5 x 10^9^/L (without growth factor support for the past 14 days) c. Platelet count more or equal 75 x 10^9^/L (without growth factor or platelet stimulating agents for the past 14 days) d. Adequate hepatic function per local laboratory reference range as follows: i. Aspartate aminotransferase (AST) ≤ 2.5 x upper limit of normal (ULN); ii. Alanine aminotransferase (ALT) ≤ 2.5 x ULN iii. Total bilirubin ≤ 1.5 x ULN, except in subjects with congenital bilirubinemia, such as Gilbert syndrome (direct bilirubin ≤ 1.5 x ULN).Isolated bilirubin ≥1.5xULN is acceptable if bilirubin is fractionated and direct bilirubin <35%. e. Subjects must have adequate renal function as demonstrated by eGFR ≥30 mL/min/ 1.73 m2 as calculated by Modified Diet in Renal Disease (MDRD) formula f. Spot urine (albumin/creatinine ratios (spot urine) <500 mg/g (56 mg/mmol) g. Corrected serum calcium ≤ 14 mg/dL (≤3.5 mmol/L); or free ionized calcium < 6.5 mg/dL (<1.6 mmol/L)	7. Participant has had major surgery ≤ 4 weeks prior to initiating study treatment. Kyphoplasty is not considered a major surgery.
8. A female participant is eligible to participate if she is not pregnant or breastfeeding, and at least one of the following conditions applies: a. Is not a woman of childbearing potential (WOCBP) b. Is a WOCBP and using a contraceptive method that is highly effective (with a failure rate of <1% per year), preferably with low user dependency (as described in Appendix 14.1.4) before and during the intervention period and for at least 5 months after the last dose of study intervention and agrees not to donate eggs (ova, oocytes) for the purpose of reproduction during this period. The investigator should evaluate the effectiveness of the contraceptive method in relationship to the first dose of study intervention. OR A WOCBP must have a negative highly sensitive serum pregnancy test (as required by local regulations) within 24 h before the first dose of study intervention and agree to use a highly effective method of contraception before and during the study and for 5 months after the last dose of IMP.	8. Participant must not use contact lenses while participating in this study. Bandage contacts may be prescribed by an eye care professional if needed.
9. Male participants are eligible to participate if they agree to the following during the intervention period and for 6 months after the last dose of study treatment to allow for clearance of any altered sperm: a. Refrain from donating sperm PLUS either: b. Be abstinent from heterosexual intercourse as their preferred and usual lifestyle (abstinent on a long term and persistent basis) and agree to remain abstinent. OR c. Must agree to use contraception/male condom plus partner's highly effective method, failure rate < 1% per year	9. Participant has any evidence of active mucosal or internal bleeding or other gastrointestinal disease that may significantly alter the absorption of oral drugs.
10. All subjects must agree to refrain from donating blood while on study drug and for 28 days after discontinuation from this study treatment.	10. Participant has evidence of cardiovascular risk including any of the following: a. Evidence of current clinically significant uncontrolled arrhythmias, including clinically significant ECG abnormalities such as 2nd degree (Mobitz Type II) or 3rd degree atrioventricular (AV) block b. History of myocardial infarction, acute coronary syndromes (including unstable angina), coronary angioplasty, or stenting or bypass grafting within three (3) months prior to Screening. c. Class III or IV heart failure as defined by the New York Heart Association functional classification system [NYHA, 1994] d. Uncontrolled hypertension e. Left ventricular Ejection Fraction ≤ 50%
11. All subjects must agree not to share study medication.	11. Participant has known immediate or delayed hypersensitivity reaction or idiosyncratic reactions to IMPs or drugs chemically related to IMPs, or any of the components of the study treatment
12. All prior treatment-related toxicities (defined by National Cancer Institute- Common Terminology Criteria for Adverse Events (NCI-CTCAE), version 5.0) must be ≤ Grade 1 at the time of enrolment except for alopecia.	12. Participant has an invasive malignancy other than disease under study within 5 years before trial inclusion, except o Adequately treated in situ carcinoma of the cervix uteri or the breast; o Basal cell carcinoma of the skin or localized squamous cell carcinoma of the skin; o Prostate cancer Gleason grade 6 or lower AND with stable Prostate Specific Antigen (PSA) levels off treatment; o Previous malignancy with no current evi-dence of disease, and which was confined and surgically resected (or treated with other modalities) with curative intent and unlikely to impact survival during the duration of the study.
	13. Participant is pregnant or lactating
	14. Participants who have had prior allogeneic stem cell transplant.
	15. Participants with symptomatic amyloidosis, active POEMS syndrome (polyneuropathy, organomegaly, endocrinopathy, monoclonal plasmaproliferative disorder, skin changes) or active plasma cell leukaemia at the time of screening.
	16. Participants with any serious and/or unstable pre-existing medical, psychiatric disorder or other conditions (including lab abnormalities) that could interfere with participant’s safety, obtaining informed consent or compliance to the study procedures.
	17. Subject is known to be seropositive for human immunodeficiency virus (HIV) or hepatitis B (defined by a positive test for hepatitis B surface antigen (HBsAg) or antibodies to hepatitis B surface and core antigen (anti HBs and anti HBc respectively), or hepatitis C (anti-HCV antibody positive or HCV RNA quantitation positive).
	18. Current immune or inflammatory conditions requiring immunosuppressive treatment (e.g. systemic lupus erythematosus, rheumatoid arthritis).
	19. Subject must not have received any live vaccines within 8 weeks prior to first dose of study treatment.
	20. Subject must not use or anticipate the use of prohibited medications or foods during study participation.
	21.Subject has a history of or show any signs of known meningeal/central nervous system involvement by myeloma.
	22. Evidence of other clinically significant uncontrolled condition(s) including, but not limited to: a. Uncontrolled and/or active systemic infection (viral, bacterial or fungal) requiring treatment. b. Any concurrent medical or psychiatric condition or disease (eg. uncontrolled diabetes, acute diffuse infiltrative pulmonary disease) that is likely to interfere with the study procedures or results, or that in the opinion of the investigator, would constitute a hazard for the participation in this study.
	23. Subject is known or suspected of not being able to comply with the study protocol (eg. because of alcoholism, drug dependency, or psychological disorder). Subject has any condition for which, in the opinion of the investigator, participation would not be in the best interest of the subject (e.g., compromise the well-being) or that could prevent, limit or confound the protocol-specified assessments.
	24. Treatment with any of the following within 7 days prior to the first dose of study drug: a. moderate or strong cytochrome P450 3A (CYP3A) inhibitors b. moderate or strong CYP3A inducers
	25. Administration or consumption of any of the following within 3 days prior to the first dose of study drug: a. grapefruit or grapefruit products b. Seville oranges (including marmalade containing Seville oranges) c. star fruit
	26. Participation in any other clinical trial (with the exclusion of observational studies)

The first patient was included in the BELI(E)VE trial in April 2024.

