### Study outcomes and endpoints

The primary endpoint is defined as (I) percentage (number) of patients with dose-limiting toxicities (DLTs) with DLTs defined as: (a) prolonged neutropenia grade 4 for more than ten days, (b) prolonged thrombocytopenia grade 4 for more than seven days, (c) any grade 4 non-hematologic toxicity, (d) and any grade 3 reported non-hematological toxicity, which is assigned with a possible relationship to the applied study drugs as reviewed by the Data Safety Monitoring Board (DSMB); and (II) the percentage (number) of participants with adverse events (AEs), changes in clinical signs and laboratory parameters. AEs will be graded according to Common Terminology Criteria of Adverse Events (CTCAE) v5.0.

Secondary efficacy endpoints are overall response rate (ORR), rates of IMWG responses, minimal residual disease (MRD) negativity (sensitivity 10^− 5^) rate, PFS, duration of response (DOR), and health-related quality of life assessments as a patient-reported outcome.

Assessment of circulating tumor cells (CTC), investigations of mitochondrial activity, and single-cell analyses for immunophenotyping will be investigated as exploratory biomarkers.

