### Sample size

In Phase I of the dose escalation, we employ the standard 3 + 3 design to limit the number of patients exposed to the belantamab mafodotin and venetoclax combination and ensure safety. This approach involves forming cohorts of three patients each. The initial cohort receives the starting dose, followed by subsequent cohorts receiving the second through fourth doses, aiming to evaluate 12 patients (Fig. 2). Dexamethasone is included for cohorts three and four to optimize the triplet combination.

If none of the three patients in a cohort experiences dose-limiting toxicities (DLT), another three patients will be treated at the next higher dose level. However, if one of the first three patients experiences DLT, three more patients will be treated at the same dose level. For the dose escalation phase I, 12–24 patients will be allocated to the trial. The RP2D will be identified based on the safety and preliminary efficacy in phase I.

Phase I will be followed by a cohort expansion phase IIa, which will evaluate the clinical activity of the combination treatment with RP2D in 25 more patients.

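### Inclusion 7c does not exclude a platelet count supported by transfusion, although 7a does so for haemoglobin, and such a count could feed a thrombocytopenia DLT unrelated to the study drugs

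*Protocol article*

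**What the plan says.** Protocol article, Table 1, inclusion 7, sets three blood-count limits, each with its own condition on support:

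- 7a, haemoglobin at least 8.0 g/dL: "without transfusion of red blood cells for the past 14 days".
- 7b, neutrophils at least 1.5 x 10^9/L: "without growth factor support for the past 14 days".
- 7c, platelets at least 75 x 10^9/L: "without growth factor or platelet stimulating agents for the past 14 days".

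Transfusion is mentioned in 7a and nowhere else in the article. None of the three items says from which date the 14 days are counted. The section on trial assessments allows baseline assessment within 30 days before treatment.

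The section on study outcomes and endpoints lists as DLT item (b) "prolonged thrombocytopenia grade 4 for more than seven days". Item (b) carries no condition on the baseline count. The wording on possible relationship to the study drugs, with DSMB review, follows item (d), on grade 3 non-haematological toxicity.

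On phase I, the section on sample size says: "This approach involves forming cohorts of three patients each". No DLT among three leads to the next level; one DLT among three adds three more patients at the same level.

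**The concern.** The three items share one evident purpose, that the qualifying count should be the patient's own. Item 7a closes the transfusion route for red cells. Item 7c closes the drug route for platelets but leaves open transfusion, the direct way to raise a platelet count. Read literally, a transfused count of 75 x 10^9/L or more satisfies it.

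Two things are at stake. The first is safety: a patient could enter with a true platelet count below the limit that the protocol sets, on a regimen for which the discussion names thrombocytopenia among the most concerning venetoclax events. The second is the dose decision. DLT item (b) asks neither what the count was before treatment nor whether the drugs caused the fall, so thrombocytopenia that was present before dosing can be scored against the dose level. Because thrombocytopenia is also an expected drug effect, a false event would be hard to tell from a true one. Each escalation decision rests on three to six patients, so a single misattributed event carries weight.

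**Working it through.** **Plan's own figures.** Four levels of three patients give 4 x 3 = 12. Four levels of six give 4 x 6 = 24. With phase IIa, 24 + 25 = 49. The stated 12–24 and up to 49 reproduce and are not affected by this point.

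**Does another criterion close the gap?**

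- Inclusion 12 limits prior treatment-related toxicity to grade 1 at enrolment. It does not reach low platelets caused by the disease, and it does not say that the graded count must be untransfused.
- Exclusion 16 covers serious or unstable conditions, including laboratory abnormalities, that could interfere with safety. It rests on judgement.
- Exclusion 22b covers concurrent conditions that the investigator considers a hazard. It rests on judgement.
- Exclusion 23 covers conditions that could confound the assessments. It rests on judgement.

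None of them requires an untransfused platelet count.

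**Model for one dose level.** Let p be the true DLT probability per patient and q = 1 − p. The level is passed on 0/3, or on 1/3 followed by 0/3:

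P(escalate) = q³ + 3pq² × q³

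The article states only the 0/3 and 1/3 steps. Escalating after 1/6 and stopping at two or more DLTs are assumed here as the standard 3+3 rule.

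Without false DLTs, at p = 0.20: 0.512 + 0.384 × 0.512 = 0.709. At p = 0.10 the result is 0.906, and at p = 0.30 it is 0.494.

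**If exactly one of the first three patients carries a false DLT.** The 0/3 path is gone. The other two must be free of DLT, and so must the next three:

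P(escalate) = q² × q³

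| True DLT rate | No false DLT | One false DLT in the first three | Two or more DLTs in the first three (without → with) |
|---|---|---|---|
| 10% | 0.906 | 0.590 | 0.028 → 0.190 |
| 20% | 0.709 | 0.328 | 0.104 → 0.360 |
| 30% | 0.494 | 0.168 | 0.216 → 0.510 |

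This table is conditional on the event having happened. It says nothing about how likely the event is.

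**Weighted by an assumed frequency.** Let f be the share of patients who enter on a transfused count and then show a false DLT. The documents do not give f, so 2%, 5% and 10% are assumed, independently of true DLTs. The DLT probability per patient becomes p' = 1 − (1 − p)(1 − f), which is put into the first formula. At p = 0.20:

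- f = 2%: p' = 1 − 0.80 × 0.98 = 0.216
- f = 5%: p' = 1 − 0.80 × 0.95 = 0.240
- f = 10%: p' = 1 − 0.80 × 0.90 = 0.280

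| f | At least one false DLT in three patients, 1 − (1 − f)³ | P(escalate), p = 10% | p = 20% | p = 30% |
|---|---|---|---|---|
| 0 | 0 | 0.906 | 0.709 | 0.494 |
| 2% | 0.059 | 0.875 | 0.674 | 0.466 |
| 5% | 0.143 | 0.824 | 0.622 | 0.425 |
| 10% | 0.271 | 0.730 | 0.536 | 0.360 |

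**The case against.** The strongest reply is that this is a drafting asymmetry with a narrow consequence. A false DLT needs grade 4 thrombocytopenia for more than seven days, not merely a count that slips below 75 x 10^9/L. The patient must therefore be at or near grade 4 without transfusion, be transfused up to the limit, and pass inclusion 12 and exclusions 16, 22b and 23. The last of these, on conditions that confound assessments, comes close to describing the case. The documents give no frequency and do not say how soon a transfused count would fall back. Handling of baseline cytopenia in DLT assessment may also be set out in the full protocol.

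Most of this stands. It makes the event uncommon and its size unknown. It does not close the gap: the other criteria act by judgement or cover only treatment-related toxicity, while 7c is the explicit platelet rule and is silent on transfusion. Nor is this simply detail lost in condensing the protocol. Table 1 gives the criteria at length, and 7c does contain a condition on support, only an incomplete one.

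A reader might infer that a patient admitted on a transfused count will go on to register a false DLT, or that one such event halts escalation. The documents support neither. The first depends on how low the untransfused count is. On the second, the section on sample size answers one DLT in three by adding three patients; stopping takes a further DLT, and that rule is itself assumed.

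**Conclusion.** The point holds as an internal inconsistency with a possible, not a certain, effect on the dose decision. As written, 7c admits a transfusion-supported platelet count, 7a does not admit the equivalent for haemoglobin, and no other criterion requires an untransfused platelet count.

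At a true DLT rate of 20%, the loss in escalation probability is 0.035, 0.087 or 0.173 (0.709 less 0.674, 0.622 or 0.536) for assumed false-DLT shares of 2%, 5% or 10%. The steeper fall to 0.328 applies only if one of the first three patients is taken as certain to carry a false DLT, and should not be read as the expected effect. All these figures rest on the assumed frequency, independence between patients, and the standard 3+3 completion rule. The direction is not in doubt: any false DLT makes a level look more toxic than it is. The correction is worth making because it is cheap, not because the effect has been shown to be large.

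**What to change.** Reconcile 7c with 7a, so that the qualifying platelet count must also be free of platelet transfusion over the same 14-day look-back, and state that the look-back runs from the qualifying sample. This governs only which count qualifies a patient. It places no restriction on transfusion that is clinically needed.

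The cost is one clause in Table 1 and the loss of a few transfusion-dependent patients, who would become ineligible. The stated sample sizes do not change.
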